### Trial design

The RiY feasibility trial is a UK school-based, assessor-blinded, two-arm randomised controlled trial (RCT). The feasibility trial will be conducted over two to three school academic years with an interim analysis planned at the end of Academic Year 1. The findings of the interim analysis will inform possible changes required to improve operational delivery in subsequent academic years. The study will be carried out in secondary schools in West Yorkshire serving a diverse population with high dental needs. Up to five participating schools will be targeted for this study.

This intervention will be a multicomponent complex intervention comprising two main parts: (1) a short classroom-based oral health education session including three interactive workshops; (2) a reinforcement session including three interactive workshops (YUK-Oral Bugs). Participants in the control group will receive the classroom-based oral health education session after the final follow-up assessments have been completed to avoid contamination of the data collection, but access will be ensured for all to the main RiY session, so that no one is disadvantaged.

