#### Randomisation

Only Group 1 participants (11–13-year-olds) will be randomised to receive intervention or control on a form level at a 2:1 or 3:1 ratio. As it is a feasibility trial, it will be a convenient proportion based pragmatically on the school’s form structure, timetabling, and availability of our team to oversee it in the individual participating schools.

The size of year group in each participating school will vary, but group allocation will allow for approximately two-thirds of the participants to receive the intervention and the remaining one-third as a control group.

An independent allocator will be given the recruitment numbers per class to perform the randomisation and then inform the schoolteachers of the randomisation allocation.

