The use of NQD could be seen as a limitation of the study data collection. However, great lengths have been taken to train, calibrate and up-skill them to be competent assessors. They are working completely within their professional scope; plaque scoring and bleeding on probing are all commonly used clinical indices. If RiY progresses to a full trial, follow-up would require more complex ICDAS scoring and full consideration would be given to having trained and calibrated clinicians for ICDAS scoring to ensure the highest standards of data integrity. Nonetheless, NQD offer a fantastic sustainable approach to deliver school-based dental public health research. The benefits to these NQD are being explored further in a separate study by NF and NH.

The findings of this trial will inform the design of a future definitive randomised controlled trial if it is shown to be feasible. The RiY concept is expandable from Yorkshire to other geographical areas as ‘RAISED in … *[insert new locality]*’ to provide local ownership, relatability, and pride in the programme, supported by NQD in these localities could offer a sustainable approach that warrants further health economic evaluation. The current feasibility protocol is focused towards advancing mechanistic understanding with the inclusion of YUK. Preliminary health economic assessments are not possible within this RiY feasibility trial due to current funding constraints but this will be important to include in the definitive trial. At an upstream level, this could be adopted to improve oral health prevention policies and guidance to reach at-risk adolescents in areas of high oral health inequality.

Progression to main trial will be based mainly on recruitment and retention, but with other considerations that may influence modifications or remedial action, if needed prior to progression (Table 2). Facilitators and barriers to recruitment and data collection will be identified and strategies will be refined and tested in subsequent year 2 (3 if required) to further inform the main trial.

**Table 2 Tab2:** Progression criteria to progress to full trial

	**Automatic progression**	*Progression with modification if appropriate*	*Remedial action with key stakeholders/advisory group*	
**Recruitment** % of target number of 11–13-year-old participants recruited (~240 participants (~*n* = 48/school)	** > 75%**	> *50–*< *75%*	< *50%*	
Recruitment of schools *n* = 4 (numbers enrolled)	** > 75%**	> *50–*< *75%*	< *50%*	

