**Retention** % of recruited participants with follow up data	** > 65%**	> 40–< 65%	< 40%	
% of recruited schools with follow up data	** > 65%**	> 40–< 65%	< 40%	
**Randomisation:** % of contamination in the control group (whether feasible to randomise by class or by school)	** > 75%**	> *50–*< *75%*	< *50*	

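### The contamination row of the progression criteria runs backwards: high contamination of controls earns automatic progression and low contamination calls for remedial action

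*Protocol article*

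**What the plan says.** Table 2 in the Discussion of the protocol article has three outcome columns, in this order: "Automatic progression", "Progression with modification if appropriate" and "Remedial action with key stakeholders/advisory group". The Randomisation row is labelled as the percentage "of contamination in the control group (whether feasible to randomise by class or by school". Its cells, in the same column order, are above 75%, between 50% and 75%, and below 50.

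The two recruitment rows carry the same cut-offs in the same direction. The participant retention row, the percentage "of recruited participants with follow up data", has lower cut-offs (65% and 40%) but also runs from high to low. In all of those rows a high percentage is good.

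Elsewhere the protocol treats contamination as something to prevent. Under Trial design, control classes receive their session only "after the final follow-up assessments have been completed to avoid contamination of the data collection". Under Randomisation, pupils are allocated "on a form level at a 2:1 or 3:1 ratio", so control and intervention forms sit in the same school.

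**The concern.** A percentage of contamination is a measure where low is good, yet the row has the bands of measures where high is good. Applied literally, it gives the wrong decision at both ends: a clean control group is sent for remedial action and a heavily contaminated one proceeds with class-level randomisation unchanged.

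The row's own label says what it is for: whether the main trial can randomise by class or must randomise by school. No other criterion with a numeric threshold bears on that choice. The acceptability of randomisation appears among the feasibility outcomes, but without a cut-off. The row is also due to be used. The Quantitative analysis section says interim results will be set against the progression criteria, and the Trial design section places the interim analysis at the end of the first academic year, to inform changes in later years.

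**Working it through.** **1. The row as a decision rule.** Inputs are the column order and the three cells of the Randomisation row in Table 2. The second column below applies the row as printed. The third applies the same cut-offs to the percentage of controls free of contamination (100 minus the contamination percentage). The fourth keeps the label and swaps the first and last bands.

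| Contamination | As printed | Read as % free of contamination | Label kept, bands swapped |
|---|---|---|---|
| 0% | remedial | automatic | automatic |
| 40% | remedial | modification (60% free) | automatic |
| 60% | modification | remedial (40% free) | modification |
| 76% | automatic | remedial (24% free) | remedial |
| 100% | automatic | remedial (0% free) | remedial |

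As printed, exactly 50% and exactly 75% fall in no band. At 40% contamination the three readings give three different decisions, so knowing that the row is reversed does not tell the reader which rule was intended.

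**2. What the printed rule means in pupils.** Inputs are the target of about 240 participants (Table 2) and the 2:1 or 3:1 ratio (Randomisation section).

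- 2:1 gives 240/3 = 80 controls. Automatic progression needs more than 0.75 × 80 = 60 contaminated.
- 3:1 gives 240/4 = 60 controls. Automatic progression needs more than 0.75 × 60 = 45 contaminated.

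**3. Illustration of the cost to a main trial.** The protocol gives no main-trial sample size and no dilution model, so this step rests on an assumption. Let a share c of control pupils be contaminated and receive a fraction b of the intervention effect. The observed difference shrinks by the factor 1 − bc, and the sample size needed for the same power grows by 1/(1 − bc)².

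- b = 1, c = 0.25: 1/0.75² = 1.78
- b = 1, c = 0.50: 1/0.50² = 4
- b = 1, c = 0.75: 1/0.25² = 16
- b = 0.5, c = 0.75: 1/0.625² = 2.56

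Under these assumptions the automatic-progression band starts where a class-randomised trial would need about 2.6 to 16 times the sample of an uncontaminated one.

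**4. Could it be a reading fault?** This is unlikely. The row has three cells in the same order as the four rows above it, and the first is in bold like theirs. No text defines the percentage the other way round.

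**The case against.** The reversal itself is hard to dispute. The case on the other side is about its consequences.

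- **Weight of the row.** The Discussion says progression rests chiefly on recruitment and retention, and a sensible team would not treat zero contamination as a failure. This stands, and it makes literal misuse less likely. It does not settle which rule applies at intermediate values such as 40%.
- **Other evidence on the unit of randomisation.** Acceptability of randomisation, operational delivery to both groups and stakeholder feedback will also inform the choice. This stands: the row is the only numeric criterion, not the only source of information.
- **The multipliers.** They assume that contamination is a share of pupils who gain a fixed fraction of the benefit, which the protocol does not say. Smaller spillover gives smaller factors, and the clustering cost of randomising by school is left out. This stands. The figures are illustrative and are not a net comparison of class with school, but the reversal does not depend on them.
- **Sending the worst band to school-level randomisation.** The third column leaves the remedy to stakeholders and advisers. Naming the school as the fallback unit is nevertheless consistent with the row's own parenthesis, which poses exactly that choice.
- **Reading the row as a trigger to switch units.** This does not rescue it. High contamination would then call for a design change, which is the opposite of automatic progression.

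**Conclusion.** The concern holds. The Randomisation row of Table 2 is reversed or mislabelled, and as printed it gives the wrong decision at both extremes. This follows from the text alone and needs no assumption beyond contamination being undesirable, which is the protocol's own position. The likely cause is a label slip or cut-offs carried over from the recruitment rows, but the article does not show which. The size of the harm to a main trial is conditional: a 16-fold sample size at 75% contamination if contaminated controls gain the full effect, 2.56-fold if they gain half. The row should be corrected before it is used, because a progression rule whose direction is settled after the data are seen is no longer pre-specified.

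**What to change.** Amend the one row in either of two ways:

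1. Relabel it as the percentage of control participants with no exposure to the content of the RiY sessions before follow-up, and keep the bands; or
2. Keep the label and reverse the bands, for example below 25% to progress with class randomisation, 25% to 50% to modify, and above 50% for the worst band. These are the cut-offs that option 1 implies, and the sponsor should confirm that they are the ones intended.

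In either case, state that the worst band points to randomisation by school in the main trial, assign the boundary values to a band, and add the missing percentage sign in the last cell. If the interim comparison has already been made, record which reading was used.

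The cost is one reworded table row. Both versions need some measure of control exposure, but so does the present label, so the correction adds nothing to trial conduct.

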**Other considerations that may influence modifications/remedial actions:**				
• Recruitment and retention of 16–18-year-old students *n* = 10–12/school/sixth form college • Confirmation of feasibility of consent process (analysis of rates for questionnaire/dental assessments and saliva sampling) • Confirmation of operational delivery to intervention and control groups and suitability of embedding educational component within curriculum Confirmation of feasibility to collect clinical data, questionnaires, dental checks and saliva • Assessment of data quality of questionnaire response completion • Confirmation of positive effect on toothbrushing at approx. 10–12 weeks: a. Pre- and post-intervention (individual) b. By randomisation group				

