**Discussion:**

The findings of the feasibility trial will dictate whether the project is scalable and can be delivered to multiple schools regionally and nationally. The findings will also show whether it is an effective method to provide oral health education for 11–13-year-old adolescents when delivered collaboratively by trained 16–18-year-old peer leaders.

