## Methods/design

### Trial aims and objectives

The aim of this feasibility trial is to establish RiY with its peer-to-peer delivery model within the secondary school setting supported by newly qualified dentists (NQD) as a feasible, effective and sustainable approach to improve oral health awareness, skills (toothbrushing) and behaviours in adolescents from underserved at-risk communities.

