### Efficacy research question

5. Is there a change in oral health knowledge, skills, and toothbrushing-related oral indices of peer recipients and peer leaders participating pre to post the RiY complex intervention? (To support future trial design).

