#### Study population and setting

A feasibility trial allows identification of key challenges with implementing a complex intervention and operational delivery in the school setting that is unfamiliar with undertaking RCTs. This trial aims to recruit up to five UK secondary schools with an integrated Sixth Form/Sixth Form Colleges and their feeder secondary schools. A formal sample size calculation was not used for this feasibility trial. Rather a pragmatic approach will be adopted informed by the systematic review of Parker et al. [37] looking at health interventions in schools, guidelines developed by Teresi et al. [38] for designing feasibility and pilot studies, and the BRIGHT trial that worked with similar aged adolescent participants delivering an oral health intervention in schools randomised by forms within year groups [5] using a target of *n* = 60 per year group/school. The focus in RiY is on practical considerations, needing to work within a tight budgetary constraint, but considering primarily the number of participants needed to reasonably evaluate feasibility goals of recruitment and retention of students alongside collecting process evaluation data on logistical components of working in school settings located with catchment to an underserved community with high oral health inequalities and often high ethnic diversity, alongside needing to assess the training of peer leaders that is a novel delivery approach of RiY’s oral health promotion. For 11–13-year-old participants, the target recruitment will be at least four classes per school with all students invited (class size is typically *n* = ~30 students/class) achieving *n* = ~240 participants (~*n* = 48 11–13-year-old participants/school); it is expected that this sample size will provide sufficient data to inform a future main trial. This trial will work closely with teachers to ensure that the intervention has minimal interruption to normal school curriculum and timetabling.

For 16–18-year-old peer leaders, the target recruitment will be *n* = ~50 peer leaders (10–12 participants per school/college).

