To facilitate evaluation of the programme and explore added benefits to the RiY-peer leaders, they will be invited to provide written optional consent to undergo dental assessments, saliva sampling (as part of the YUK-Oral Bugs citizen science project), complete oral health questionnaire and quiz. This will allow researchers to evaluate if RiY-peer leaders receive oral health benefits as a result of taking part in the programme. The participants will be fully informed with a detailed Participant Information Sheet and provided with the opportunity to refuse/withdraw without being disadvantaged in any way.

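### Uncontrolled pre-post change should not count as confirming an effect on toothbrushing; the between-arm contrast is valid but imprecise, so the effectiveness wording claims too much

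*Protocol article*

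**What the plan says.** All references are to the protocol article.

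- **Table 2, other considerations:** one item is "Confirmation of positive effect on toothbrushing at approx. 10–12 weeks: a. Pre- and post-intervention (individual) b. By randomisation group". It has no threshold or estimate and no rule for what follows if (a) and (b) disagree.
- **Discussion, text before Table 2:** "Progression to main trial will be based mainly on recruitment and retention", "with other considerations that may influence modifications or remedial action, if needed prior to progression".
- **Efficacy research question:** it asks about change in knowledge, skills and "oral indices of peer recipients and peer leaders participating pre to post the RiY complex intervention". No between-arm contrast appears, and a bracketed note says the purpose is to support future trial design.
- **Effectiveness wording:** the abstract says "The findings will also show whether it is an effective method to provide oral health education". Trial aims and objectives sets out to establish the programme "as a feasible, effective and sustainable approach to improve oral health awareness". Trial feasibility questions also asks whether it is effective.
- **Design and analysis:** "A formal sample size calculation was not used for this feasibility trial" (Study population and setting). Forms are randomised 2:1 or 3:1, and only the 11–13-year-olds are randomised (Randomisation). The analysis is descriptive (Quantitative analysis).
- **Peer leaders:** of their optional assessments, the text under Group 1 participants consent says "This will allow researchers to evaluate if RiY-peer leaders receive oral health benefits as a result of taking part in the programme".

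**The concern.** The trial pays for a randomised control arm, yet one of the two ways of judging an effect on toothbrushing, and the whole of the efficacy question, ignore it. Change from baseline in treated pupils mixes the intervention effect with whatever would have happened anyway. The protocol itself supplies sources of such change. Controls still receive the standard dental curriculum from teachers (Intervention), and all participants brush their teeth and are examined at both time points (Group 1 data collection). Regression to the mean matters too if individual pupils' changes are read. The YUK biofeedback section recognises the issue for saliva, where control samples are to pick up background influences in the school, but the toothbrushing item does not carry that reasoning over.

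Limb (b) is the right comparison, but the trial was not sized for it, so asking it to confirm an effect asks too much. At stake are a misread secondary consideration, which may feed into decisions on modification or remedial action, and effectiveness conclusions that the data cannot carry. For peer leaders, who have no control group, a before-after change cannot be attributed to taking part.

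**Working it through.** **Inputs from the protocol article.** Target about 240 pupils, about 48 per school, up to five schools: 5 × 48 = 240, which reproduces the target. No alpha, power, effect size, SD or intraclass correlation (ICC) is stated, so there is no power figure to reproduce. At least four classes per school gives about 5 × 4 = 20 forms, or 240/20 = 12 pupils per form. Allocation is 2:1 or 3:1. Table 2 puts automatic progression above 65% retention; 0.65 × 240 = 156 is the lower scenario.

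**Assumptions.** Two-sided alpha 0.05, ICC 0 to 0.10, pre-post correlation 0.5, true effects of 0.2, 0.3 and 0.5 SD, shared background improvement of 0.1 to 0.3 SD.

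**Limb (a): intervention arm alone, no true effect.** At 2:1 the arm has 160 pupils. In SD units the standard error of the mean change is √(2(1 − 0.5)/160) = 0.079.

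- Shared improvement 0.1 SD: P(mean change in the improving direction) = Φ(0.1/0.079) = 0.90; P(nominally significant improvement) = 0.24.
- 0.2 SD: 0.99 and 0.72.
- 0.3 SD: above 0.99 and 0.97.

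With 104 pupils (65% of 160) the pairs are 0.85 and 0.17, 0.98 and 0.53, and above 0.99 and 0.86. These figures ignore form clustering of change, which would make the probabilities less extreme. The bias does not depend on sample size: a shared 0.2 SD improvement enters the pre-post estimate as 0.2 SD.

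**Limb (b): between arms.** SE = √(DE × (1/n₁ + 1/n₂)), with DE = 1 + (m − 1) × ICC and m = 12, or 7.8 at 65% retention. Example at 2:1, 240 pupils, ICC 0.10: DE = 1 + 11 × 0.10 = 2.10; SE = √(2.10 × (1/160 + 1/80)) = 0.198; half-width 1.96 × 0.198 = 0.39 SD.

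| Pupils, ratio | 95% CI half-width (SD), ICC 0 / 0.05 / 0.10 | Difference detectable with 80% power (SD) | Power for 0.3 SD |
|---|---|---|---|
| 240, 2:1 | 0.27 / 0.33 / 0.39 | 0.38 / 0.48 / 0.56 | 59% / 42% / 33% |
| 240, 3:1 | 0.29 / 0.36 / 0.42 | 0.42 / 0.52 / 0.61 | 52% / 37% / 28% |
| 156, 2:1 | 0.33 / 0.39 / 0.43 | 0.48 / 0.55 / 0.62 | 42% / 33% / 28% |
| 156, 3:1 | 0.36 / 0.42 / 0.47 | 0.52 / 0.60 / 0.67 | 37% / 29% / 24% |

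Across these scenarios power is 13% to 31% for 0.2 SD and 55% to 95% for 0.5 SD.

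**Does baseline adjustment rescue it?** Take 192 followed up (128 and 64), 20 forms, 9.6 per form, correlation 0.5, ICC 0.01 / 0.05 / 0.10. SE = √((1 − 0.5²) × (1 + 8.6 × ICC) × (1/128 + 1/64)) = 0.138 / 0.159 / 0.181. With t on 18 degrees of freedom the half-widths are 0.29 / 0.33 / 0.38 SD, and power for 0.3 SD is 54% / 43% / 35%. Adjustment helps, but the picture is the same.

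**The case against.** The strongest reply is that this is a feasibility trial that says so. Feasibility is the primary outcome, the clinical indices are secondary, the efficacy question is there to support future design, and low power in a trial that disclaims a power calculation is no error. Limb (a) also does not stand alone: a trend common to both arms would show as no difference under (b). The word confirmation recurs for several items in the same list and need not mean a hypothesis test. The precision figures rest on assumed inputs, and model details belong in a statistical analysis plan that is not shown.

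Most of this stands, and it limits the weight of the point. It does not remove it. Limb (a) is still listed as a way to confirm an effect, with nothing to say that (b) takes precedence. A before-after change does not supply the between-arm effect on which a main trial is designed, so the stated purpose argues for the randomised contrast. And the aim, a feasibility question and the abstract speak of effectiveness.

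Three stronger readings are tempting but not supported:

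- A reader might infer that a shared improvement would carry the trial forward to the main study. The Discussion rests progression mainly on recruitment and retention, and this item may only influence modification or remedial action.
- A reader might infer that any favourable sign counts as confirmation. No such rule is written.
- A reader might infer that peer leaders' baseline follows their training. The text ties their data collection to the younger pupils' schedule, but that schedule (Table 1) is not visible here, so the timing cannot be judged.

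The peer-leader sentence states an aim to evaluate benefit rather than a finding; the fault is the causal phrase applied to an uncontrolled group.

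**Conclusion.** The point holds as one of wording and choice of contrast, with limited effect on decisions. Limb (a) and the efficacy question, as written, would credit to the intervention any change shared by both arms; this follows from the design and needs no assumed figure. Limb (b) is valid, but under the assumed inputs its 95% confidence interval extends roughly 0.3 to 0.5 SD either side of the estimate, and 80% power is reached only for differences of about 0.4 to 0.7 SD. It therefore cannot reliably confirm or exclude small to moderate effects. The conclusion is less absolute for large effects, since 0.5 SD would be detected with 55% to 95% power. The effectiveness statements in the abstract, the aim and the feasibility questions go further than this design allows.

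**What to change.** - **Table 2:** remove (a) as evidence of effect and keep pre-post change as a descriptive summary by arm. Recast (b) as the between-arm difference at follow-up, adjusted for baseline and allowing for form clustering, reported with a 95% confidence interval to inform main-trial planning, not as a condition to be confirmed. The model itself can sit in the statistical analysis plan.
- **Efficacy research question:** pose it for peer recipients as a difference between randomised arms.
- **Peer leaders:** describe their change over time without attributing it to taking part.
- **Abstract, aim and feasibility questions:** speak of estimating potential effect, and leave effectiveness to the definitive trial.

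The cost is wording only, since the plaque and gingival indices and the questionnaire are already collected at baseline and after the intervention in both arms. The downside is a less ambitious stated conclusion.
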